### Outcomes

*Primary outcomes,* which are assessed by questionnaires (survey data), are the quality of the patient-physician communication and patient informedness (Table 2). It is analysed whether values in the IG differ significantly from the CG.

**Table 2 Tab2:** Primary outcomes, instruments and measurement points

	t_0-physician_	t_0-patient_	t_1-patient_	t_2-patient_	t_1-physician_	t_2-physician_
Quality of the patient-physician communication (patient)						
Shared Decision-Making Questionnaire (SDM-Q-9) [38]			X			
Questionnaire on the communication behaviour of physicians (KOVA) [39]			X			
Scale “Satisfaction” of the P.A.INT-questionnaire [40–43]			X			
Quality of the patient-physician communication (physician)						
Scale “Effective and open communication” of the KOVA [39]^a,b^	X				X	X
Scales “Empathy”, “Openness and coherence”, “Positive regard and appreciation”, “Contact barriers” and “Satisfaction” of the P.A.INT-questionnaire [40–43]^a^	X				X	X
One Item of the Man-Son-Hing scale. [44]^a^	X				X	X
Shared Decision-Making Questionnaire (SDM-Q-Doc) [45, 46]^a^	X				X	X
Informedness (patient)						
Self-reported knowledge questionnaire^c^		X		X		
Self-reported knowledge global question^c^			X			
Perceived informedness questionnaire^c^				X		
Perceived informedness global question^c^			X			

^a^Instruments will be adapted so that physicians assess their communication behaviour across consultations

^b^Instrument will be adapted for assessing the communication from physician’s perspective

^c^These instruments will be developed for the project. The questionnaires will be checked for understandability and acceptance in a cognitive pretest using one-to-one interviews with eight patients having experienced back pain [47]

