#### Sample size calculation

A priori calculation of the sample size to test the IG’s superiority to the CG in primary outcomes (comparison of adjusted mean values in two groups) was performed with the software *“Power and Precision*”. We used an effect size of 0.30, power of 0.80 and a Bonferroni adjustment (5% / 2 = 2.5%) due to the multiple testing of two primary outcomes. The design effect due to clustering of the practices [30] is DE = 1 + 0.01 × (10–1) = 1.09 with an assumed intra-cluster correlation of 0.01 [31] and a number of cases per cluster of *N* = 10. With a 2:1 distribution in the IG and CG, a sample size of *N* = 320 (IG) and *N* = 160 (CG) without design effect and *N* = 349 (IG) and *N* = 175 (CG) with design effect was calculated. Due to an expected dropout of approximately 35% a sample size of *N* = 537 (IG) and *N* = 270 (CG) is necessary. However, health economics evaluation including a budget impact analysis requires a relatively large variance of cost values (150% standard deviation). Based on a power of 0.80, an alpha level of 5% and an effect size of 30%, the number of cases is *N* = 590 (IG) and *N* = 295 (CG) without design effect and *N* = 643 (IG) and *N* = 322 (CG) with design effect. Given the assumed dropout of approximately 35%, this results in the desired recruitment target of *N* = 1.000 (IG) and *N* = 500 (CG).

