### Generation and concealment of allocation sequence and implementation of allocation

The participating practices are allocated in a 2:1 ratio of IG to CG. The allocation will be stratified by number of participating physicians within a practice (1 physician vs. 2–4 physicians vs. more than 4 physicians). The allocation sequence will be computer generated and concealed until time of allocation. The UHE will recruit the practices, while the MPS will generate the allocation sequence. The UHE will send a list with the research numbers of the practices and the stratification characteristics to the MPS which adds the information about group allocation according to the randomly generated sequence.

The UHE will inform the practices about their allocation. This procedure ensures that neither the recruiting nor the analysing institutes can influence that a particular practice will be allocated to either IG or CG.

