### Statistical methods

#### Analysis of patients‘questionnaire data

Based on the analysis of the missing outcome data, simple or multiple imputation may be considered. Dropout analysis will be performed using Chi-Squared tests for nominal variables, Mann–Whitney U tests for ordinal variables and t-tests for interval variables. The significance level is set at *p* = 0.05. Special attention is paid to the hierarchical data structure of the questionnaire data. Due to the cluster randomisation, patients’ responses cannot be presumed as independent, as the patients are nested within practices. Because of this, separate two-level (patient – practice) multilevel linear models for both measurement points (t1 and t2) will be calculated. Treatment allocation (IG vs. CG) will be used as predictor variable in the multilevel linear models. The fit of the multilevel linear models are tested using amongst others the Akaike’s information criterion and Schwarz’s Bayesian criterion. Despite the randomisation a propensity score adjustment is considered in case of a potential imbalanced allocation [32]. Intraclass correlations are calculated to assess the cluster (practice) dependency of the responses.

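### The patient models name allocation as the only predictor: the randomisation stratum and available same-scale t0 values should be fixed as covariates, rather than leaving adjustment to a conditional propensity score

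*Protocol article*

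**What the plan says.** Under Analysis of patients' questionnaire data, the Protocol article plans that "separate two-level (patient – practice) multilevel linear models for both measurement points (t1 and t2) will be calculated". It continues: "Treatment allocation (IG vs. CG) will be used as predictor variable in the multilevel linear models". No t0 value, stratum or control variable is given a place in these models. The only adjustment mentioned is conditional: "Despite the randomisation a propensity score adjustment is considered in case of a potential imbalanced allocation". What counts as imbalance, and which variables would enter the score, is not stated.

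Three other places bear on this:

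- **Sample size calculation** describes the primary test as a "comparison of adjusted mean values in two groups".
- **Generation and concealment of allocation sequence** states: "The allocation will be stratified by number of participating physicians within a practice". There are three levels: one, two to four, and more than four physicians.
- **Outcomes, Tables 2 and 3** show which patient measures have a t0 value. Among the patient primary instruments only the self-reported knowledge questionnaire does (t0 and t2). Among the secondary outcomes, PEPPI, HLQ and pain VAS are taken at t0 and t2. Table 3 also lists patient control variables collected at t0: back beliefs, sociodemographic data, internet use and medical data.

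**The concern.** There are three separate issues.

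1. **Mismatch within the article.** The sample size section speaks of adjusted means. The patient analysis names an allocation-only model and makes adjustment conditional. The physician analysis in the same article does commit to adjusted comparisons and names its control variables.

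2. **Adjustment that depends on the data.** With no trigger and no covariate list, the choice between an unadjusted and a propensity-adjusted primary estimate falls after the data are seen. By the article's own account, the evaluators making that choice are not blinded. Imbalance is also foreseeable. Practices are told their allocation, and their physicians then enrol the patients, so randomising practices does not by itself balance the patients who are enrolled. Covariates fixed in advance give partial protection, limited to what is measured.

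3. **Precision given up.** Where the same scale is measured at t0 and t2, a post-only model discards prognostic information already collected. The stratum is known for every practice and is also unused.

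**Working it through.** **Step 1. Reproduce the plan's figure.** Inputs from Sample size calculation: effect size d = 0.30, power 0.80, alpha 2.5% per outcome, ratio 2:1, design effect 1 + 0.01 × (10 − 1) = 1.09, dropout 35%. Sidedness is not stated.

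Control group size = (1 + 1/2) × (z for alpha + z for power)² × SD² / d². With two-sided 2.5% and SD = 1 this is 1.5 × (2.241 + 0.842)² / 0.09 = 158.4, so 159 control and 318 intervention. The t-based version gives 160 and 320, the stated figure. One-sided 2.5% gives 131 and 262 and does not match.

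- With the design effect: 320 × 1.09 = 348.8 and 160 × 1.09 = 174.4, so 349 and 175.
- With dropout: 349 / 0.65 = 536.9 and 175 / 0.65 = 269.2, so 537 and 270.

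All stated figures reproduce with a standardised effect of 0.30 and no further variance reduction for covariates.

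**Step 2. Where an own t0 value exists.**

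| Patient measure | t0 | After t0 | Own-baseline adjustment |
|---|---|---|---|
| Self-reported knowledge questionnaire (primary) | yes | t2 | possible |
| Self-reported knowledge, global question (primary) | no | t1 | not on the same scale |
| SDM-Q-9, KOVA, P.A.INT Satisfaction (primary) | no | t1 | not possible |
| Perceived informedness, questionnaire and global question (primary) | no | t2; t1 | not possible |
| PEPPI, HLQ, pain VAS (secondary) | yes | t2 | possible |

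**Step 3. Gain from the t0 value.** With t0–t2 correlation r, the residual variance is multiplied by 1 − r², and the equivalent sample factor is 1 / (1 − r²). The article gives no r; 0.3 to 0.7 is an assumed range. The design effect is held at 1.09.

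| Assumed r | Variance factor | Equivalent sample factor | Control/intervention N before design effect | Power at 160/320 |
|---|---|---|---|---|
| 0 (unadjusted) | 1.00 | 1.00 | 159/318 | 80% |
| 0.3 | 0.91 | 1.10 | 145/290 | 84% |
| 0.5 | 0.75 | 1.33 | 119/238 | 91% |
| 0.7 | 0.51 | 1.96 | 81/162 | 98% |

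**Step 4. Gain from the stratum.** At ICC 0.01 and 10 patients per cluster, the variance of an arm mean is proportional to 0.99 + 10 × 0.01 = 1.09. If the stratum explained all between-practice variance, the factor would be 0.99 / 1.09 = 0.908, a reduction of at most about 9%. If it explained a quarter, the factor would be (0.99 + 0.075) / 1.09 = 0.977, about 2%.

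**Step 5. Power at the actual target.** The cost outcome sets recruitment at 1000 and 500. After 35% dropout, 650 and 325 remain. The effective control number is 325 / 1.09 = 298.2. The standard error in SD units is √(1.5 / 298.2) = 0.0709, and 0.30 / 0.0709 = 4.23. Power is Φ(4.23 − 2.24) = 97.7%, and the effect detectable with 80% power is 3.083 × 0.0709 = 0.22. With adjustment at r = 0.5, power is 99.6% and the detectable effect 0.19.

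**The case against.** The strongest reply is that this is a condensed article. Saying that allocation will be a predictor does not say that nothing else enters. The t0 control variables in Table 3 and the reference to adjusted means both suggest that adjustment was intended, with the covariate list left to a fuller document. That is fair as to the missing list. But the article does state a model, and it states that adjustment is conditional on imbalance. That is a choice, and a better one is available at no cost.

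Several stronger readings are tempting but not supported:

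- **That t0 values exist for the primary outcomes in general.** Only one of the seven patient primary instruments has one. Patient-rated communication, one of the two primary domains, has none.
- **That the trial loses needed power.** It does not, on its own assumptions (step 5). The article also offers no basis for r, and the one primary instrument concerned has yet to be developed.
- **That the sample size relies on adjustment.** The stated numbers reproduce without any separate covariate term.
- **That omitting the stratum invalidates the standard errors.** Omission tends to make them conservative, and the possible gain at ICC 0.01 is small.
- **That propensity adjustment is wholly post hoc, or should be banned.** It is announced in advance; what is open is when it applies and with which variables. If selective recruitment affects many characteristics, a score over the collected control variables may add useful protection. No inflation of the error rate has been quantified here.

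**Conclusion.** The point holds as a matter of pre-specification and precision. The stated patient models use allocation alone, leave out a known stratification factor for all patient outcomes, and leave out the own t0 value for four measures, one of them primary. The only adjustment is conditional and undefined, which sits badly with the adjusted means in the sample size section.

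The precision at stake is about 9% to 49% of the variance of the t2 effect for those four measures, over an assumed r of 0.3 to 0.7. The stratum adds at most about 9%, at ICC 0.01 and 10 patients per cluster. For patient communication and perceived informedness no own-baseline gain is possible. The change also gives some protection against measured imbalance from unblinded recruitment after allocation. It repairs no power shortfall: about 98% power for d = 0.30 is already there if the article's ICC and dropout hold.

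**What to change.** State the primary patient model as allocation + three-level randomisation stratum + own t0 value where one exists + random practice intercept. Then:

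- Use the own t0 value for self-reported knowledge, PEPPI, HLQ and pain VAS at t2.
- For SDM-Q-9, KOVA, P.A.INT Satisfaction and perceived informedness, add the stratum and, if wanted, a short list of the t0 control variables already collected, fixed before the data are seen.
- Give a simple rule for missing t0 values, so that a patient with an outcome but no t0 value is not dropped by default.
- Move any propensity-score adjustment to a sensitivity analysis with named covariates, so that the primary estimate does not depend on observed balance.
- Bring the patient analysis and the sample size section into line on whether the comparison is adjusted.

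The cost is a change to the model text. All the variables are already collected or known from randomisation, and the sample size need not change. The one practical burden is handling missing t0 values, which the rule above covers.

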#### Analysis of physicians‘questionnaire data

The data analysis is primarily exploratory. The primary outcomes will be analysed using inferential statistics methods. IG and CG will be compared across the three measurement points. Statistically adjusted comparisons of means between IG and CG as well as across the three measurement points (using propensity scores) will be conducted. The characteristics of the practices and the user data of the online platform will be used as control variables. Before the calculations, the missing data processes, singular missing data and the drop-out of patients will be analysed. Recommendations regarding the handling of missing data in order to correct information biases will be considered [33]. If data is missing completely at random or missing at random, missing data will be imputed using the expectations-maximation algorithm. Moreover, there will be sensitivity analyses to assess the influence of missing data processes.

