### Participants and recruitment

Together with the *Bavarian Association of Family Physicians and General Practitioners,* the *Institute of General Practice at the University Medical Center Erlangen* (UHE) will recruit a total of 150 general practitioners (GP) from practices in Northern Bavaria. Two-thirds of the practices are randomized to the IG and one third to the CG. If a GP practice expresses interest after being invited to participate in the study, it receives information concerning the study, regulations for enrolling in the intervention program, and participation documents for the GP practice and the patients. After written consent to study participation and enrolment in the intervention program, the practice is formally included in the GAP trial. The UHE passes on registration data to the *Bavarian State Association of company health insurance fund*, which is responsible for the cooperation with the participating company health insurance funds. Over five quarters (July 2018 to September 2019), the GP practices are to recruit a total of 1000 patients for the IG and 500 for the CG. With an average share of at least 20% BKK insured persons, 900 patients per practice license in Bavaria and a back pain prevalence of almost 30%, the resulting recruitment potential is 50 to 60 patients per physician. The fact that physicians receive reimbursement for recruitment and patients receive a book voucher will facilitate sufficient recruitment.

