#### Procedures for physicians

Physicians in IC and CG fill out the primary outcome questionnaires at the following time points: before intervention (before accessing the portal (t0), directly after recruiting the last patient (t1), and 3 months after recruiting the last patient (t2). Data from the CG is gathered concurrently. Physicians in the IG are interviewed online, physicians in the CG via an online survey or, where appropriate, paper-pencil questionnaires (hybrid survey). Structural features of practices are collected once in an initial questionnaire in both IG and CG. After the intervention (t1) in the IG, usage, usability and accordance of information and information needs are surveyed. To test for enduring use, the usage of the platform is again measured at t2. Physicians in the CG continue to perform their usual consultation routines. The participating physicians of the IG and CG are given an incentive for study participation by the UHE at the end of the survey period. The incentive is calculated according to the number of recruited patients per physician (34 € per participating patient in IG and CG). Additionally, the physicians in the IG receive 40 € once per patient for the first consultation using the portal. The study protocol does not determine any limitations or specifications for further consultations or the care of the patients. Physicians of the IG are asked to use the portal during the consultation according to the instructions and the consultation guidance. To ensure appropriate usage of the portal, the UHE sets up a telephone hotline for the physicians in case of difficulties or questions. During the initial phase, the institute contacts each IG physician at least once proactively, and offers support. This proactive contact is made step by step. First, the physicians are contacted by email and asked whether support is needed. If there is need for support, telephone contact is offered and, if necessary, a personal visit is made. As an adherence indicator the frequency of portal usage per physician is measured via web analytics. 25 IG physicians are randomly selected and interviewed by the Institute of Medical Psychology and Medical Sociology (MPS) after inclusion of the last patient in semi-structured telephone interviews on portal acceptance, quality and practicability (implementation, supportive factors and barriers) and the perception of their own communication behaviour as well as the subjective evaluation of the consultation guidance.

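### Physician-rated communication: the planned three-point, propensity-score comparison does not name the physician's t0 score or the randomisation stratum as covariates

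*Protocol article*

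**What the plan says.** Table 2 lists physician-rated quality of communication among the primary outcomes. Every instrument in that block (the KOVA scale, the P.A.INT scales, the Man-Son-Hing item and the SDM-Q-Doc) is marked at t0, t1 and t2. Under Procedures for physicians, both arms complete these questionnaires, and t0 comes before access to the portal. Each physician therefore has a true baseline on each scale.

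Analysis of physicians' questionnaire data first calls the analysis mainly exploratory, then says that the primary outcomes will be analysed inferentially. It compares the arms across all three time points: "Statistically adjusted comparisons of means between IG and CG as well as across the three measurement points (using propensity scores) will be conducted". On covariates it says: "The characteristics of the practices and the user data of the online platform will be used as control variables". It names no model and does not list what enters the propensity score.

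Practices are the randomised unit: "Two-thirds of the practices are randomized to the IG and one third to the CG". Allocation is stratified by the number of participating physicians in the practice, in three classes. That factor does not appear by name in the physician analysis.

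For patients, the article plans separate models at t1 and t2, and propensity adjustment is only considered if allocation turns out imbalanced. For physicians, t0 is one of the compared occasions and propensity scores are the stated method.

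**The concern.** Self-rated communication probably differs stably between physicians, so a physician's t0 score is likely to be the best available predictor of the t1 and t2 scores. In a randomised trial a propensity score has no systematic confounding to remove. It can recover the precision that baseline adjustment offers only if the t0 score is in it, and the text does not say that it is. Portal use arises after allocation, and control physicians have no portal access, so that control variable cannot stand in for a baseline.

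Comparing means across three points also leaves open what the treatment effect is. It could be the difference at t1, the difference at t2, a change from t0, or a group effect that includes t0, when no effect can yet exist. These options have different precision. With only 150 physicians at 2:1 the choice matters, because a chance difference at t0 is plausible with about 50 controls and stays in any estimate that does not account for it.

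**Working it through.** **The plan's own figure.** The Sample size calculation section uses an effect of 0.30, power 0.80 and alpha 2.5% for a "comparison of adjusted mean values in two groups", at 2:1. It does not state sidedness. With two-sided alpha, the smaller group needs (2.2414 + 0.8416)² × (1 + 1/2) / 0.30² = 158.4, so 159 and 318, against the stated 160 and 320. With the design effect, 160 × 1.09 = 174.4 and 320 × 1.09 = 348.8, which gives the stated 175 and 349. Dividing by 0.65 gives the stated 270 and 537. One-sided 2.5% gives 131 and 262, which does not match. These figures concern patients. No sample size or power is given for the physician comparison.

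**Inputs for physicians.** d = 0.30 and two-sided alpha 0.025 are carried over from that section. There are 150 physicians. The split of about 100 to 50 is inferred from the 2:1 allocation of practices. The t0-t1 correlation r is not in the document, so it is an assumption, shown from 0.3 to 0.7 and taken as equal between all pairs of occasions. Variances are taken as equal, and the other control variables as explaining no outcome variance. Clustering of physicians in practices is ignored. The only value given, "with an assumed intra-cluster correlation of 0.01", belongs to a design effect for 10 cases per practice and says nothing about physicians.

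**Formula.** Two-sample noncentral-t power with noncentrality δ / √(V × (1/100 + 1/50)) = δ / √(0.03 V), on 148 degrees of freedom (score SD = 1):

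- t0 unused (t1 only): δ = 0.30, V = 1. Noncentrality 0.30 / 0.1732 = 1.73.
- Change from t0: δ = 0.30, V = 2(1 − r).
- t1 adjusted for t0: δ = 0.30, V = 1 − r².
- Group mean over t0, t1 and t2: δ = 0.30 × 2/3 = 0.20, V = (1 + 2r)/3.

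| Analysis | r = 0.3 | r = 0.5 | r = 0.7 |
|---|---|---|---|
| t0 unused | 30.0% | 30.0% | 30.0% |
| Change from t0 | 21.5% | 30.0% | 49.0% |
| Mean over t0, t1, t2 | 25.0% | 20.1% | 16.8% |
| t1 adjusted for t0 | 33.0% | 39.8% | 56.5% |

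A normal approximation gives the same values to within one percentage point.

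**Gain from t0 adjustment.** Against t0 unused: 3, 10 and 27 points. Against change from t0: about 12, 10 and 7 points. Against the three-point mean: 8, 20 and 40 points. At r = 0.5 the variance falls by 25%.

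**Detectable effect at 80% power** (normal approximation, 3.083 × √(0.03 V)): 0.53 without t0, 0.46 with t0 at r = 0.5, and 0.38 at r = 0.7.

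**If the 35% dropout applied to physicians** (65 versus 33): 20% without t0, against 26% at r = 0.5 and 38% at r = 0.7 with it.

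**The case against.** A reader might infer that the plan discards the t0 score and adjusts by propensity scores in its place, and so certainly loses power. The text does not support that. It does not say what enters the score, and t0 could be in it. A comparison across three occasions may well mean a group-by-time contrast with t0 as reference, which uses t0 within each physician. The loss against t0 adjustment is then about 7 to 12 points over the range of r shown. It is about nil if t0 is in the score or the baselines are modelled as common to both arms. Nothing states that the group effect is averaged over t0, t1 and t2, so the 17% to 25% figures describe the least favourable reading and not a stated plan.

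It is also fair to say that the article calls the physician analysis mainly exploratory, claims no power for it, and is a condensed account whose covariate lists may be completed in an analysis plan. The gain rests on an assumed correlation, and even the adjusted analysis stays well below 80% power at d = 0.30.

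These points limit the size of the concern but do not remove it. The article does fix the occasions compared, the adjustment method and a list of control variables, and t0 and the stratum are not named in that list. The primary hypothesis covers ratings by general practitioners, Table 2 lists them as primary, and the primary outcomes are to be tested inferentially.

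**Conclusion.** The point holds as one of an under-specified and probably less efficient analysis, not as a demonstrated loss. On the stated assumptions, adjusting the post-baseline score for t0 gives about 33% to 57% power, and no reading of the planned comparison in the table does better at the same r. The advantage ranges from about nil to several tens of points, depending on what the three-point comparison turns out to mean and on r. Clustering within practices would lower all the powers. The main limit is having 150 physicians, which no covariate cures. The change is worth making because the baseline is already collected and the gain costs almost nothing.

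**What to change.** In Analysis of physicians' questionnaire data, make the main analysis of the physician-rated primary outcomes a model of the t1 and t2 scores. Its terms would be allocation, time, allocation-by-time, the physician's own t0 score on the same scale, the randomisation stratum and a random effect for practice, with the two scores of one physician allowed to correlate. A longitudinal model with the baseline constrained equal across arms would serve as well. Report the IG-CG difference at t1 and at t2, and do not count t0 as an outcome occasion in the treatment contrast. Handle missing t0 scores with the imputation already planned. Keep the propensity-score comparison as a sensitivity analysis, and state which variables enter the score.

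The cost is a change of wording, with no new data or participants. The downside is a few degrees of freedom: one for the t0 score and two for the three-class stratum.

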## Methods

The GAP trial uses a prospective multi-centre, cluster-randomized parallel group design in order to evaluate whether the use of the GAP portal on back pain is superior to routine care. The GAP project consists of three phases. (1) Within the pilot phase, the portal will be tested for usability by physicians and patients and adapted according to the pilot findings (Additional file 1: Development and piloting of the GAP portal). (2) The main trial (second phase) evaluates the effects on pre-defined outcomes in general practitioners and patients with back pain (Table 1). (3) Within the third phase, the potential benefit of web-based information for health problems other than back pain will be analysed (Additional file 2: Expanding of the GAP portal).

**Table 1 Tab1:** PICO question of the GAP trial

Research Question	What are the effects of using the back pain internet portal compared to standard care in patients with back pain?
Population	150 general practitioners and 1500 back pain patients in Northern Bavaria
Intervention	Using the portal during (physician) and after (patient) the consultation.
Comparison	Routine consultation (no use of the portal)
Outcomes	1. Physicians‘and patients’ informedness 2. Physician-patient-communication 3. Patients‘health literacy and self-efficacy expectation 4. Days of sick leave 5. Back pain related health costs

*Hypothesis on primary outcomes:* (1) After the consultation, the informedness and the quality of the physician-patient communication are rated significantly higher by general practitioners and patients who use the portal (intervention group, IG) than by those who do not (control group, CG, consultation as usual).

*Hypotheses on secondary outcomes:* (2) 3 weeks after the consultation, the patients’ informedness, health literacy and self-efficacy are significantly higher among those who use the portal than among those who do not. (3) 3 months after consultation, the number of days of sick leave as well as the utilization of health system resources is significantly lower among patients who use the portal than among those who do not.

*Design:* Prospective cluster RCT with pre-, post- and one follow-up-measurement and process evaluation.

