Control variable (web analytics)							
Portal use by patients		Throughout the intervention phase (after consultation)					
Portal use by physicians	Throughout the intervention phase						

^a^Instrument will be adapted so that the physicians assess the portal

^b^only intervention group

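### The physician IG–CG comparison is to be adjusted for portal use, which is measured after randomisation and is the intervention itself

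*Protocol article*

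**What the plan says.** In the protocol article, the section on the analysis of physicians' questionnaire data opens by calling that analysis primarily exploratory. It continues: "The primary outcomes will be analysed using inferential statistics methods". The group comparison is then described: "Statistically adjusted comparisons of means between IG and CG as well as across the three measurement points (using propensity scores) will be conducted". The next sentence names the adjustment variables: "The characteristics of the practices and the user data of the online platform will be used as control variables". Nothing in the section confines the user data to the IG.

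Table 3 (Outcomes) repeats the role. Under "Control variable (web analytics") it has one row for patients' portal use and one for physicians'. The patient row is timed "Throughout the intervention phase (after consultation"); the physician row spans the whole intervention phase.

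Elsewhere the same measure has a different role. Procedures for physicians says: "As an adherence indicator the frequency of portal usage per physician is measured via web analytics". Process evaluation plans to link the user data to the questionnaires. Table 1 (Methods) defines the intervention as "Using the portal during (physician) and after (patient) the consultation" and the comparator as "Routine consultation (no use of the portal").

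The section on the analysis of patients' questionnaire data enters allocation as the predictor in two-level models and names no portal-use term.

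**The concern.** A covariate in a randomised comparison should be fixed before allocation can affect it. Logged portal use is not. The physicians' t0 questionnaire precedes access to the portal, so all use follows it. The Abstract gives portal access to the IG, and the portal needs a login, so use in the CG is zero by design or has no value at all.

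The protocol asks whether the portal is superior to routine care. A model holding portal use constant answers another question: how IG physicians who did not use the portal would compare with CG physicians. Any benefit that comes through use moves out of the group coefficient and into the usage coefficient.

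At stake are the physician-rated communication scales. They are listed as primary in Table 2, and the primary hypothesis in Methods covers ratings by general practitioners.

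**Working it through.** **No stated figure is in dispute.** The point concerns what the model estimates. The plan's own sample size for the primary outcomes does reproduce: effect 0.30, two-sided alpha 2.5%, power 0.80 and 2:1 allocation give 318/159 against the stated 320/160. That calculation counts patients, 10 per cluster. No power is stated for the physician comparison.

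**Inputs from the article.** 150 general practitioners; practices allocated 2:1, so about 100 IG and 50 CG physicians if practice sizes balance; planning effect 0.30 SD.

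**Assumptions, not in the article.** Use is 0 in the CG. In the IG it follows a gamma distribution with mean 1 and variance 0.5 (SD about 0.7). The residual SD is 1, physicians are independent, and a share *s* of the effect scales linearly with use. The remainder is the same for every IG physician.

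**Step 1: what the adjusted coefficient estimates.** Use does not vary in the CG, so the usage slope *b* comes from the IG alone. The group coefficient is the IG line extrapolated to zero use, minus the CG mean:

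adjusted effect = total effect − *b* × mean use

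With *b* = *s* × 0.30 and mean use 1, this is 0.30 × (1 − *s*).

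**Step 2: standard error.**

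- Without use: √(1/100 + 1/50) = √0.03 = 0.173.
- With use: √(1/100 + 1/50 + 1²/(100 × 0.5)) = √0.05 = 0.224.
- Ratio: √(0.05/0.03) = 1.29.

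**Step 3: simulation check** (4,000 runs per row, 100 IG and 50 CG physicians, two-sided 5% test).

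| Share scaling with use | Formula | Simulated, adjusted | SE without / with use | Rejection without / with use |
|---|---|---|---|---|
| 0% | 0.300 | 0.299 | 0.172 / 0.224 | 39.7% / 26.5% |
| 25% | 0.225 | 0.224 | 0.173 / 0.225 | 40.4% / 16.6% |
| 50% | 0.150 | 0.147 | 0.174 / 0.226 | 40.6% / 10.5% |
| 75% | 0.075 | 0.078 | 0.174 / 0.225 | 41.0% / 6.3% |
| 100% | 0.000 | 0.000 | 0.176 / 0.225 | 39.3% / 5.0% |

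Without use in the model, the estimate stays at about 0.30 in every row. The SE ratio runs from 0.224/0.172 = 1.30 to 0.225/0.176 = 1.28. A run of 200,000 units at 2:1 with SD of use 0.7 gave adjusted effects of 0.153 (half) and 0.002 (all), with SE ratios of 1.27 to 1.28.

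**Step 4: direction.** The table assumes that use and outcome share no other causes. If they do, *b* absorbs that association as well. By the formula in step 1, the adjusted effect is pushed down if better communicators use the portal more, and up if they use it less.

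**The case against.** The best defence is that the sentence is loosely worded. The section plans comparisons between arms and also across measurement points, and does not say which of them the control variables serve. Logs exist only for the IG, the article itself treats use as adherence, and the process evaluation uses the same data. An IG-only analysis may have been meant. That is conceivable, but the text does not say so. The sentence directly follows the adjusted IG–CG comparison, Table 3 repeats the label, and the process evaluation is a separate use. An analyst following the text would fit the wrong model.

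A second objection is that the analysis is primarily exploratory and no power is claimed for it. This stands, and it limits the weight of the point. It does not remove it, because the same section has the primary outcomes tested inferentially.

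Three stronger readings are tempting but not supported:

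- **Patient results.** A reader might infer from Table 3 that the patient comparison is also adjusted for portal use. Table 3 lists measures and specifies no model, and the patient models name no such term.
- **Propensity score.** A reader might infer that user data enter the propensity score, so that the arms no longer overlap. Propensity scores and control variables stand in separate sentences, and no covariates for the score are listed.
- **A working portal reported as ineffective.** This is the worst case. The adjusted effect of 0.00 follows by construction when all of the effect is assumed to scale with use. When none does, the estimate is unbiased and only precision is lost.

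**Conclusion.** The point holds for the physician comparison. As written, the group coefficient would not estimate the total effect of allocation on outcomes that Table 2 lists as primary. This follows from the timing and nature of portal use and needs no numerical assumption.

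The size does need assumptions, and the documents supply neither the distribution of use nor the share of the effect that runs through it. In the illustration, a true 0.30 SD is estimated as anything from 0.30 down to 0.00, with a standard error about 27–30% larger. Shared causes of use and outcome could shift the estimate either way. The rejection rates also ignore clustering by practice and dropout, so they are comparisons and not forecasts. For patients, only the Table 3 label needs correcting.

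**What to change.** In the section on physicians' questionnaire data, remove the platform user data from the control variables of the IG–CG comparison. Limit those variables, and any propensity score, to pre-randomisation covariates such as practice characteristics, the stratification factor (number of participating physicians per practice) and the t0 score. The article places t0 before portal access; it should be confirmed that it also precedes disclosure of allocation.

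Relabel the two portal-use rows of Table 3 as adherence or process variables. Use portal data only in a separately labelled IG-only dose-response or process analysis.

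The cost is one rewritten sentence and two table labels. No new data are needed and no sample size changes. An instrumental-variable analysis is not needed to repair this. It would require allocation to act only through logged use, which is doubtful with unblinded, self-rated outcomes.
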